### Theoretical Model for the Intervention

The present study builds on the overarching proposition that having bystanders intervene more often and more constructively in everyday bullying and harassment episodes, preferably before the bullying situations have escalated, should help to reduce the occurrence and prevalence of this pertinent problem over time. The present intervention study then builds on the theory of planned behavior (TPB; Ajzen, 1991) to achieve this. The TPB proposes three determinants of a person’s intentions, behavior, and any following behavioral changes, attitude, subjective norms, and perceived behavioral control. These three factors will be seen as proximal and mediating outcomes, while observed and perceived exposure to bullying, including observed social climate, will be the more distal and final focal outcome. In our context, attitude will be addressed by the very nature of the intervention, that is, creating awareness and changes in attitudes regarding the existence and nature of workplace bullying and one’s own attitudes and perceived typical bystander behavior in such situations. The intervention is further designed to alter participants’ subjective norms by increasing the perceived social pressure to perform constructive bystander behavior in such situations. Lastly, by showing when and how bystanders may intervene constructively (Ajzen and Madden, 1986; Ajzen, 1991), the intervention should alter individuals’ perceived behavioral control in specific situations, the latter implying the extent to which the behavior is perceived to be under volitional control. Thus, developing a psychosocial climate in the organization where individual attitudes and social norms foster constructive bystander behavior, while also enhancing the employees’ perceived behavior control as bystanders, is hypothesized to be crucial in combating workplace bullying in organizations.

Accordingly, in addition to investigate any changes in bullying and harassment in the working environment, the present study will examine whether attitudes, social norms, and perceived behavioral control of those who have received an intervention called “Intervene,” will be changed and possibly influence bystander behavior in bullying situations. Ultimately, the intervention should reduce the occurrence of bullying and harassment and improve the social climate at work. As such, we hypothesize the following regarding these proximal outcomes:

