1.Those who have received the intervention will have a change in **outcome variables (behavior)** from T1 to T2 as compared to those in the control group:1.1.Those who receive the intervention will have an increase in *observed workplace bullying* from T1 to T2 as compared to those in the control group due to an increased awareness.1.2.Those who receive the intervention should report lower exposure to bullying behaviors, as compared to those in the control group.1.3.Those who receive the intervention will be more likely to *intervene when observing workplace bullying* from T1 to T2 as compared to those in the control group.2.Those who receive the intervention will have a change in **independent variables (attitudes, norms, perceived control, and social climate)** from T1 to T2 as compared to those in the control group:2.1.Those who receive the intervention will have an increase *in their attitudes toward intervene constructive when observing workplace bullying* from T1 to T2 as compared to those in the control group.2.2.Those who receive the intervention will have an increase in *perceived bystander norms* from T1 to T2 as compared to those in the control group.2.3.Those who receive the intervention will have a more positive view of the *social climate* in the working group from T1 to T2 as compared to those in the control group.2.4.Those who receive the intervention will have an increase in perceived *informal surveillance* from T1 to T2 as compared to those in the control group indicating an increase in social anti-bullying norms in the working environment.2.5.Those who receive the intervention will have an increase in *perceived bystander behavior control* from T1 to T2 as compared to those in the control group.3.From T2 to T3 the control group, which will receive the intervention after T2, will show the same results of the abovementioned hypothesis as the intervention group did from T1 to T2.

An overview of the relationships studied in this intervention is given in Figure 1.

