**Figure 2 fig2:**
[figure not shown]
A description and flow-chart of the contents and main elements of the intervention.

The intervention comprises a preparatory part in order to anchor the program among managers, health and safety representatives, and labor union representatives. This initial preparatory part aims at increasing ownership to the program at all management levels and among elected health and safety representatives, and labor union representatives, thereby ensuring that key stakeholders contribute to successful implementation and follow up of the intervention.

The program is further divided into **three elements:**

1. A **planning meeting** at the workplace/department prior to the program with managers at the department level, the local labor union representative, the local health and safety representative, and a local HR representative.2. A 3-h **group session** with work-teams of 15–30 employees with their supervisors, managers, and elected health and safety representatives as participants.3. A **follow-up session** with department managers, those line managers, and elected health and safety representatives that participated in element two with the aim of following up ideas and suggestions for bystander guidelines created by employees in element two.

These three elements will now be described in more detail:

The first element consists of an initial meeting with the department manager and HR representatives laying the foundation for how to divide the department into groups used in the second part of the program and to prepare the department manager for his or her active role as host in the main intervention.

The second element and main part of the intervention, the group sessions, concentrates on the participants’ awareness of, knowledge about, and perceptions related to workplace bullying and harassment and of the possible role of bystanders. The main focus is on the opportunities for bystanders to intervene constructively in such situations. The sessions have a duration of 3 h and are divided into four consecutive parts with short breaks between each section.

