1. An opening part is led by the department manager, starting with a 5-min video talk by the executive vice-president on the importance of the intervention to the company. Thereafter, the department manager provides a talk on the importance of the issue, providing also information about the organization’s policies and procedures for handling workplace bullying and its complaints and investigation procedures. Thereafter, the consultant leading the intervention has a 15–20-min presentation on the issue of workplace bullying and the role of bystanders and their possible role taken in a bullying scenario. This part is intended to last for 45 min.2. The second part is made up of two 10 min films describing two typical bullying scenarios, each followed by group discussions on the role of the bystanders in these films and how the bystanders intervened and could have intervened more constructively than they actually did. This part adds up to approximately 40 min.3. The third part includes a scenario quiz focusing on possible bullying and harassment situations asking how participants themselves think they would have handled the situation (by using an interactive presentation tool), followed by group discussions on how their work team usually reacts and should react to these different kinds of examples of bullying and harassment. This part is intended to last for 40 min.4. The last part consists of a group discussion with the aim of developing suggestions and norms for how one should react as a bystander and how one may intervene in specific situations with bullying and negative acts. Each group writes up their suggestions and ideas. This last part is intended to last for about 30 min, including a closing talk from the department manager of the way forward, the importance of the issue at stake, and his/her summation of the 3-h session.

The third element is a group session for line managers and a health and safety representative. The aim of this session is to develop local guidelines for the department on how bystanders could and should intervene when observing acts of bullying and harassment, based on the suggestions derived from the “Grip inn/Intervene!” group sessions. Lastly, an action plan for the implementation and follow up of these bystander guidelines are discussed and developed. The session will be led by the department manager and a consultant.

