#### Bullying and Negative Acts

*Workplace Bullying-*Exposure to bullying behaviors from colleagues in the workplace is measured with the nine-item version of the *Negative Acts Questionnaire-Revised* (NAQ-R) inventory (Notelaers et al., 2018). NAQ-R describes negative and unwanted behaviors that may be perceived as bullying if occurring on a regular basis. All items are formulated in behavioral terms and focus on the mere exposure to inappropriate behaviors while at work with no references to the term bullying (Einarsen and Nielsen, 2015). The scale has proven reliable in former studies, calculating Cronbach’s Alpha for the nine-item version to be 0.86 (Einarsen et al., 2018). In addition, three items from the original version are included, as these three items addresses negative acts related to sexual behavior. Example items are “Spreading of gossip and rumors about you” and “Being shouted at or being the target of spontaneous anger or rage.” The respondents are asked to indicate how often they have been exposed to each specific item in the questionnaire at their present worksite during the last 6 months. Response categories range from 1 to 5 (“never,” “now and then,” “monthly,” “weekly,” and “daily”).

Observed bullying will be measured with the use of the *Bergen Bullying Indicator* (Einarsen and Raknes, 1991), a five-item instrument which measures the degree to which bullying is perceived to constitute a problem at the workplace (e.g., “Bullying at my workplace reduces our efficiency”). The scale has been used in former studies, which has reported Cronbach’s Alpha to be 0.93 (Hauan and Klaveness, 2018). A five-point Likert scale, ranging from totally agree to totally disagree, was applied.

*Observed and witnessed bullying* will also be measured with a single item; “Over the past 4 months, have you observed anyone being bullied in your team/department?”, accompanied by five answer alternatives with regard to frequency of experience (“No, never,” “Yes, a couple of times,” “Yes, every now and then,” “Yes, several times per week,” and “Yes, daily”).

The *observed bullying* question is followed by another question which measure whether or not the respondent intervened if (s)he observed bullying in her/his team. The response categories are as following: “Yes,” “no,” and “I have not observed any bullying activities.”

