*Self-labeled victimization* from workplace bullying will be measured with a single item used in several previous studies on bullying (Olweus, 1991; Einarsen and Skogstad, 1996; Solberg and Olweus, 2003; Nielsen et al., 2011). The respondents are asked “*Have you been subjected to bullying at the workplace during the last* 4 *months?*” Response categories range from 1 to 5 (“no,” “rarely,” “now and then,” “once a week,” and “several times a week”).

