## Discussion

This project will address some important knowledge gaps in research on workplace interventions against workplace bullying, focusing on the role of bystanders in a preventive intervention. First, we refine and test a relatively short and focused intervention that may easily be implemented in many organizational contexts. Based on qualitative group interviews, there is reason to believe that such an intervention at least will be highly appreciated by those involved (Mikkelsen and Hogh, 2019). Second, we will evaluate this intervention employing a range of proximal and distal outcomes, such as participant satisfaction, prevalence of bullying both observed and experienced, changes in perceived social climate regarding interpersonal trust, and conflict management. Based on the TPB, we will particularly look at changes in attitudes, perceived behavioral control, and social norms as possible proximal and mediating factors. Third, whereas previous studies on interventions on workplace bullying have mainly used qualitative methods or inadequate designs based on quantitative methods (Escartin, 2016; Gillen et al., 2017), the present project is based on an experimental RCT design including longitudinal quantitative survey data, which is a novel approach within this field of research. Fourth, by examining mediating and moderating variables in the relationship between perceived bystander behavior control and outcomes, this project will generate novel knowledge important for extending and developing the theoretical basis of our understanding of bystander behavior, which is critical in order to adequately design upcoming studies and further interventions in this area. From an applied perspective, the current project will elucidate specific prevention and management strategies that can help organizations protect their employees against the detrimental effects of workplace bullying. The resulting knowledge will aid efforts to improve employee well-being and the overall quality of work environment. Knowledge about preventive measures against bullying among employees is important in order to protect the health, well-being, and work ability of employees, which in turn will determine the quality of the work they perform. The results of this project will help identify whether/how specific bullying prevention and harassment measures at work are associated with decreases in workplace bullying prevalence. Moreover, it will shed light on the mechanisms that may explain why such an intervention may work or not.

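### The self-labelled victimization item depends on how respondents understand bullying, which the programme sets out to change, so its contrast cannot by itself show a change in prevalence

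*Protocol article*

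**What the plan says.** Under Bullying and Negative Acts, self-labelled victimization "will be measured with a single item used in several previous studies on bullying". The item reads "Have you been subjected to bullying at the workplace during the last" 4 months, with five frequency answers. The same section measures exposure to bullying behaviours with the nine-item NAQ-R, over 6 months, and says its items "focus on the mere exposure to inappropriate behaviors while at work with no references to the term bullying".

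The sessions (The Intervention) concentrate on participants' "awareness of, knowledge about, and perceptions related to workplace bullying and harassment". They include a "presentation on the issue of workplace bullying and the role of bystanders", two films of bullying scenarios and a scenario quiz. Theoretical Model for the Intervention gives the intent as "creating awareness and changes in attitudes regarding the existence and nature of workplace bullying". Under Study Design, the location A controls and location B receive the programme 6 months after the intervention group.

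Hypothesis 1.1 expects observed bullying to rise in the intervention group "as compared to those in the control group due to an increased awareness". Hypothesis 1.2 expects lower exposure to bullying behaviours. Hypothesis 3 expects the controls to show the same results from T2 to T3. Quantitative Data Analysis and Statistics plans prevalence rates and group differences, and the Discussion lists "prevalence of bullying both observed and experienced" among the outcomes to be evaluated.

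**The concern.** The single observed-bullying item and the self-label item are built alike: both use the word, both look back 4 months, and both take a five-point frequency answer. For observed bullying the protocol reads a rise as awareness. For a person's own victimization it makes no such allowance, although the same sessions come between the two measurements.

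If training changes what workers are prepared to call bullying, the item measures something different in the two arms at T2. The controls then undergo the same change between T2 and T3, where hypothesis 3 is tested. Randomization does not protect against this, because the shift is itself an effect of treatment, and a larger sample does not reduce it.

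Bullying is a main distal outcome, and under Dissemination the company will use the findings to decide on wider implementation. The protocol does not say which measure of experienced bullying carries the prevalence claim, or which prevails if the NAQ-R and the self-label item disagree.

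**Working it through.** The protocol gives no sensitivity or specificity for the item, so there is no figure of its own to reproduce. Everything below on labelling is an illustration with assumed inputs.

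**Formula.** Reported prevalence = p × Se + (1 − p) × (1 − Sp), where p is true prevalence, Se the share of true victims who label themselves bullied, and Sp the share of non-victims who do not.

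**Break-even with Sp = 1.** A true relative fall r disappears when p(1 − r) × Se(trained) = p × Se(control), that is, when Se(trained)/Se(control) = 1/(1 − r). This does not depend on p:

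- r = 10%: ratio 1.11
- r = 20%: ratio 1.25
- r = 25%: ratio 1.33
- r = 30%: ratio 1.43

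**Example A: sensitivity rises.** Assume true prevalence of 8% in controls and 6% in the trained arm (r = 25%), Se(control) = 0.50 and Sp = 1. Controls report 0.08 × 0.50 = 4.0%. The trained arm reports:

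- Se 0.50: 0.06 × 0.50 = 3.0% (fall fully visible)
- Se 0.60: 3.6%
- Se 0.67: 4.0% (fall hidden)
- Se 0.75: 4.5% (sign reversed)

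**Example B: a higher base.** The Introduction cites a global rate of up to 15% for more severe cases. Assume 15% v 12% (r = 20%), Se(control) = 0.60 and Sp = 1. Controls report 9.0%. The trained arm reports 7.2% at Se 0.60, 8.4% at 0.70, 9.0% at 0.75 and 9.6% at 0.80.

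**A bound.** With r = 30% and Se(control) = 0.70, break-even needs Se(trained) = 0.70/0.70 = 1.00. A fall of that size cannot be reversed through sensitivity alone.

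**Example C: specificity rises instead.** Keep 8% v 6% and Se = 0.50 in both arms.

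- Controls, Sp 0.98: 0.08 × 0.50 + 0.92 × 0.02 = 5.84%
- Trained, Sp 0.98 (no shift): 0.06 × 0.50 + 0.94 × 0.02 = 4.88%, a difference of 0.96 points
- Trained, Sp 0.99 (stricter labelling): 0.030 + 0.94 × 0.01 = 3.94%, a difference of 1.90 points

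Here the apparent benefit doubles with no change in true prevalence.

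**How many self-labellers there would be.** Statistical Power expects 750–1,050 baseline respondents. Split evenly over three groups (an assumption), that is 250–350 per group. At 4% reported prevalence this gives 0.04 × 250 = 10 to 0.04 × 350 = 14 self-labellers per group. The standard error of 4.0% v 3.0% is √[(0.04 × 0.96 + 0.03 × 0.97)/n], which is 1.64 points at n = 250 and 1.39 at n = 350, before any allowance for clustering. The 1-point difference is therefore 0.6 to 0.7 standard errors.

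**Recall window of the NAQ-R.** It asks about 6 months, while Statistical Power puts 4 months between surveys. A T2 answer then reaches 6 − 4 = 2 months back before T1, so part of it describes time before the programme.

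**The case against.** The strongest reply is that the hypothesis on a worker's own exposure is already safe. Hypothesis 1.2 speaks of exposure to bullying behaviours, the term the protocol attaches to the NAQ-R, and no hypothesis names the self-label item. This stands and limits the point: the trial has a usable measure. What remains is that the analysis section and the Discussion speak of prevalence without naming the measure, while Questionnaire Instruments says effects will be assessed with the whole 74-item questionnaire.

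Three stronger readings are tempting, and the documents do not support them:

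- **That the bias runs against the programme.** Hypothesis 1.1 makes this plausible, but it concerns noticing what happens to others. The Introduction's concept of bullying is demanding (systematic, persistent, hard to defend against). Workers who come to see it that way might stop labelling minor acts, as in example C.
- **That workers are taught a definition.** The protocol describes a presentation, films, a quiz and discussion. It does not say that a definition is taught.
- **That the item carries no definition.** The questionnaire is not shown, and an article may leave out an item's lead-in text.

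Strengths and Limitations adds that changed perception of one's own exposure is the aim. That is a legitimate aim, but it does not separate changed perception from changed prevalence. The sections on response, recall, selection and contamination bias do not address a labelling threshold that differs by arm.

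It is also fair to say that so few self-labellers could hardly support a prevalence claim in any case. That is a further reason not to rest one on this item.

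**Conclusion.** The point holds as a problem of interpretation for one outcome. It is not a flaw in the test of hypothesis 1.2. The self-label contrast at T2, and the controls' change from T2 to T3, can mix true change with a labelling shift whose size and sign the documents do not allow anyone to derive. Under the assumed figures, a rise in sensitivity from 50% to 67% hides a 25% fall, and a one-point rise in specificity doubles the apparent benefit. That training changes labelling of one's own experience is an inference. It rests on the stated purpose of the sessions and on the protocol's own premise for observed bullying. The NAQ-R is much less exposed because it avoids the word. The change is worth making because it costs almost nothing and keeps a confounded contrast from being read as an effect on prevalence.

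**What to change.** 1. In Quantitative Data Analysis and Statistics, and where the Discussion speaks of prevalence, state that any claim of reduced experienced bullying (hypotheses 1.2 and 3, and prevalence) rests on the NAQ-R only.
2. Reconcile the NAQ-R's 6-month recall with the 4-month survey interval, so that a T2 answer does not reach back before baseline.
3. Report self-labelled victimization as secondary, and not as evidence of a change in prevalence by itself.
4. Show self-labelling conditional on NAQ-R score, by arm and wave, as a descriptive check only. Few events are expected, and the NAQ-R is itself measured after treatment, so people with the same score at T2 need not be comparable between arms.
5. Add differential labelling to Assessment of Potential Bias.
6. If the questionnaire does not already do so, show the same definition above the item at all waves in all groups. This would reduce the problem without removing it.

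The cost is a few sentences, one table from data already planned, a check of the recall wording and possibly one line in the questionnaire. The small downside is weaker comparability with any earlier use of the item without a definition.

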#### Social Climate at Work

Social climate will be measured by four items from climate for conflict management (Rivlin, 2001), three items from climate for psychological safety (Edmondson, 1999), and three items from Intragroup Conflict (Jehns, 1995). The scale assesses intragroup trust and perceived fairness and trust in the department’s dispute resolution and conflict management procedures, including trust in managers’ conflict management skills. These scales have been used in numerous studies, and researchers have reported the scales as reliable with Cronbach’s alpha of 0.81 for climate for conflict management (Zahlquist et al., 2019), Cronbach’s alpha of 0.86^1^ for climate for psychological safety (Koopmann et al., 2016), and Cronbach’s alpha of 0.92^2^ for intragroup conflict (Jehns, 1995). Example items are “The management handles cases of conflicts well” (conflict management climate), “It is easy to address problems and difficult issues in my work team” (intragroup trust), and “There is jealousy and rivalry between members of my work team” (intragroup conflict). In addition, a five-point Likert scale from 1 (“do not agree”) to 5 (“agree completely”) will be used for responses.

